# Preeclampsia risk prediction model for Chinese pregnant women (ChiPERM): research protocol for a randomized stepped-wedge cluster trial

**DOI:** 10.1186/s12884-022-04858-x

**Published:** 2022-06-29

**Keywords:** Preeclampsia, Placenta growth factor, Risk prediction, Aspirin, Pregnancy, Antenatal care, Stepped-wedge trial, Protocol

## Abstract

**Background:**

Despite international clinical guideline recommendations, implementation of Bayes-theorem based preeclampsia risk prediction model in first trimester among Chinese women is limited. The aim of this study is to examine the effectiveness of this risk predictive strategy in reducing the risk of preeclampsia.

**Methods:**

The study will be a randomized, stepped-wedge controlled trial conducted in eighteen hospitals in China. Stepped implementation of Bayes-theorem based risk prediction model will be delivered to hospitals in a random order to support the introduction of this prediction model of preeclampsia. A staged process will be undertaken to develop the risk prediction strategies, which comprise of: combined risk evaluation by maternal risk factors, medium arterial pressure, uterine artery pulse index and placenta growth factor during 11–13^+6^ gestational weeks, monthly follow up (including blood pressure, newly onset complications, adherence to aspirin). Repeated cross-sectional outcome data will be gathered weekly across all hospitals for the study duration. The primary outcome measures are the incidence of preeclampsia within 42 days postpartum. Data on resources expended during intervention development and implementation will be collected. The incidence of pregnancy related complications will be measured as secondary outcomes.

**Discussion:**

This will be the first randomized controlled trial to evaluate the effectiveness of the Bayes-theorem based preeclampsia risk prediction strategies in first trimester by competing risk model validation. If positive changes in clinical practice are found, this evidence will support health service adoption of this risk prediction model to reduce the risk of preeclampsia among Chinese pregnant women.

**Trial registration:**

Chinese Clinical Trials Registry, No. ChiCTR2100043520 (date registered:21/2/2021).

## Background

Preeclampsia is a common obstetrical complication, affecting 2%-8% of all pregnancies [1, 2]. It accounts for maternal and infant morbidity and mortality worldwide. Since first case report in 1978 [3], prevention of preeclampsia with aspirin has been studied for decades [4]. Its effect is inconsistent in abundant case–control, prospective cohort, or meta-analysis studies [5–12]. In the trial of low-dose Aspirin in the Prevention of Pre-Eclampsia in China (APPEC), the strategy of a dose of 100 mg aspirin daily in preventing preeclamapsia among high-risk women screened with maternal risk factors did not reduce the incidence of preeclampsia, indicating further consideration combining with maternal biophysical parameters [13]. In 2019, the International Federation of Gynecology and Obstetrics (FIGO), has recommended a Bayes theorem-based model, which integrated with maternal risk factors, mean arterial pressure (MAP), uterine artery PI (UTPI) and serum placenta growth factor (PlGF) [14]. It has provided a new era for the preeclampsia risk prediction.

Despite clear recommendations in clinical guidelines of preeclampsia risk prediction, most evidence are based in Caucasians or African Americans [5, 9–12, 15]. In the randomized controlled study-the Aspirin for Evidence-Based Preeclampsia Prevention trial based in European population, the incidence of preterm preeclampsia has been reduced by 62% for women at high risk of preeclampsia, when they take aspirin at a daily dosage of 150 mg initiated before 16 gestational week [9]. However, studies addressing the effectiveness of this Bayes theorem-based model among Chinese pregnant women are limited. There was a prospective, non-intervention, multiple centered trial conducted among 10,935 Asian women, but only approximately 700 women from Jiangsu and Yunnan province in mainland China have been recruited [16]. Thus, the effectiveness of this model across China have not been well investigated. Considering varied incidence rates among women of different race and genetic susceptibility, it is of importance to verify the performance of this Fetal Medicine Foundation (FMF) Bayes-theorem based method for Chinese women.

 Accordingly, we have initiated this randomized stepped-wedge cluster trial of Preeclampsia risk prediction model for Chinese pregnant women (ChiPERM). The aim of this study is to examine the effectiveness of this Bayes-theorem based risk prediction model in first trimester for reducing the risk of preeclampsia among Chinese pregnant women.

## Methods/design

### Study design and setting

The study will be a randomized stepped-wedge controlled trial design conducted in eighteen hospitals in mainland China. The hospitals are geographically defined groupings of antenatal facilities with common obstetric management. As shown in Fig. 1, repeated cross-sectional outcomes data will be gathered on a monthly basis across all eighteen hospitals for the duration of the study (28 months). Baseline data will be collected for each hospital from prior to the commencement of the preeclampsia risk prediction in the first hospital to the start of the intervention in each sector. Stepped implementation of a 2-month practice change of preeclampsia risk prediction will be delivered in a randomly selected order at two monthly intervals. Follow-up data will continue to be collected for all eighteen hospitals following completion of the practice change intervention. The outcomes of the trial will be determined by comparing the incidence of preeclampsia outcomes between the baseline and follow up periods for the eighteen sectors combined.

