### Risk assessment

The implementation of the Bayes-theorem based preeclampsia risk prediction will be calculated by the model of The Fetal Maternal Foundation (https://fetalmedicine.org/research/assess/preeclampsia/first-trimester). This model is derived from maternal history, MAP, UTPI and serum PlGF at 11–13^+6^ weeks. Maternal history includes age, race, height, weight, gestational week based on crown rump length (CRL), pregnancy history, use of artificial reproductive technique, smoking history, history of chronic diseases (hypertension, diabetes mellitus, renal disease), adverse pregnancy history, previous history of preeclampsia, history of autoimmune diseases, pregnancy interval over 10 years, systolic blood pressure ≥ 130mmH and (or) diastolic blood pressure ≥ 80 mmHg, obstructive sleep apnea syndrome and previous history of prenatal diagnosis such as villus biopsy and amniocentesis.

The results of laboratory examination will be collected, including levels of folic acid, vitamin B12, fasting blood glucose, blood routine, urine routine, renal function, liver function, blood lipid and coagulation function. Blood pressure is measured by validated automated devices (OMRON, HBP-1320, China) according to a standardized protocol.

Uterine artery PI (UTPI) is measured by Doppler examination of uterine arteries technique in the period from 11 to 13^+6^ gestational weeks. Since this is a common time for first-trimester ultrasound examination in mainland China, UTPI measurement in this trial is practical and available. For the first-trimester transabdominal assessment of uterine artery resistance, a midsagittal section of the uterus and cervix is obtained initially. Using color flow mapping, the transducer is gently tilted sideways, in the purpose that the uterine arteries are identified with high-velocity blood flow along the side of the cervix and uterus. The pulsed-wave Doppler sampling gate should be narrow (set at approximately 2 mm) and positioned on either the ascending or descending branch of the uterine artery at the point closest to the internal cervical os, with an insonation angle < 30◦. In order to verify that the uterine artery is being examined, the peak systolic velocity should be > 60 cm/s. The PI is measured when at least three identical wave forms are obtained. Detailed methodology can be referred to the guideline and published papers [19, 20].

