### Endpoint outcomes

Endpoint outcomes are collected at delivery and till 42 days postpartum. Pregnancy outcomes will be recorded include the incidence of preeclampsia, eclampsia, HELLP syndrome (hemolysis, elevated liver enzymes and low platelet), preterm birth, fetal growth restriction/small for gestational age, postpartum hemorrhage, placental abruption, maternal heart failure, pulmonary edema, fetal demise, fetal death, neonatal death, neonatal asphyxia, neonatal intensive care unit (NICU).

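### The baseline versus follow-up comparison is set by calendar period, but exposure is possible only at 11–13+6 weeks; read literally, about 19–33% of follow-up deliveries would be to women past the screening window when their hospital started

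*Protocol article*

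**What the plan says.** Under Study design and setting, the protocol article says that "repeated cross-sectional outcomes data will be gathered on a monthly basis across all eighteen hospitals for the duration of the study (28 months"). Baseline data for a hospital run "to the start of the intervention in each sector". The rollout is described as follows: "Stepped implementation of a 2-month practice change of preeclampsia risk prediction will be delivered in a randomly selected order at two monthly intervals". After that, "Follow-up data will continue to be collected for all eighteen hospitals following completion of the practice change intervention". The comparison is then stated: "The outcomes of the trial will be determined by comparing the incidence of preeclampsia outcomes between the baseline and follow up periods", with the eighteen sectors combined.

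The timing of exposure is fixed elsewhere. Under Risk assessment, "This model is derived from maternal history, MAP, UTPI and serum PlGF at 11"–13+6 weeks. Under Participant eligibility and recruitment, a first visit after 14 weeks is an exclusion. Under Endpoint outcomes, "Endpoint outcomes are collected at delivery and till 42 days postpartum".

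Several sections describe an enrolled cohort instead. Participant eligibility and recruitment invites women at hospitals that are conducting the intervention and screens those who consent. Aspirin intervention and Followup have recruited women seen monthly. Sample size gives an 18-month enrolment period. Statistical analysis adjusts for the risk estimated at screening.

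**The concern.** Baseline and follow-up are defined as calendar phases of a hospital, and outcomes are cross-sectional by month. Nothing in the article ties a woman's condition to where she was in pregnancy when her hospital crossed over. Screening happens early in pregnancy, while the outcome is mostly completed at or near delivery, so the two can fall in different phases. A woman at 20 weeks when her hospital starts could not have been screened, yet her delivery falls in the follow-up period.

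Counting such women as intervention outcomes mixes unexposed pregnancies into the intervention arm and pulls the estimated effect towards no difference. Because the lag spans more than one 2-month step, it also disturbs the same-month contrasts between crossed-over and not-yet-crossed-over hospitals, which are what a stepped-wedge design depends on.

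**Working it through.** **The plan's own figure.** The article gives no power calculation. Its one sample-size figure is enrolment: 15,000 × 0.70 = 10,500, which reproduces.

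**Inputs from the article.** Screening at 11 to 13+6 (13.86) weeks; 2-month steps; a 2-month practice-change block; 28 months of outcome data; 18 hospitals.

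**Assumptions.** Fig. 1 is not shown, so the number of steps and the first start are varied: 9 steps of 2 hospitals or 6 steps of 3, first start at month 0, 2 or 6. Deliveries are uniform over time. One hospital per step is left out: 18 × 2 = 36 months exceeds 28.

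**Step 1: lag from screening to delivery**, at 30.44/7 = 4.35 weeks per month.

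- Delivery at 37 weeks: (37 − 13.86)/4.35 = 5.3 to (37 − 11)/4.35 = 6.0 months.
- Delivery at 40 weeks: (40 − 13.86)/4.35 = 6.0 to (40 − 11)/4.35 = 6.7 months.
- Delivery at 34 weeks: (34 − 13.86)/4.35 = 4.6 to (34 − 11)/4.35 = 5.3 months.

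For term births the lag is therefore about three steps. The practice-change block takes up 2 months, leaving 6 − 2 = 4 months, or two steps, of follow-up affected in each hospital.

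**Step 2: unexposed share of follow-up.** For a start at month s and lag L, the unexposed months are min(28, s + L) − (s + 2), and the follow-up months are 28 − (s + 2). Sum each over the steps and divide. Every step holds the same number of hospitals, so that number cancels.

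| Layout (starts, months) | L = 5.3 | L = 6.0 | L = 6.7 |
|---|---|---|---|
| 6 steps (0–10) | 16% | 24/126 = 19% | 22% |
| 6 steps (2–12) | 17% | 24/114 = 21% | 25% |
| 6 steps (6–16) | 22% | 24/90 = 27% | 31% |
| 9 steps (0–16) | 18% | 36/162 = 22% | 26% |
| 9 steps (2–18) | 21% | 36/144 = 25% | 29% |
| 9 steps (6–22) | 28% | 36/108 = 33% | 39% |

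**Step 3: dilution in a simple before/after contrast.** Observed RR = u + (1 − u) × true RR, with u the unexposed share.

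- u = 0.25: 0.25 + 0.75 × 0.70 = 0.775, about 0.78; 0.25 + 0.75 × 0.80 = 0.85.
- u = 0.19: 0.70 appears as 0.76 and 0.80 as 0.84.
- u = 0.33: 0.70 appears as 0.80 and 0.80 as 0.87.

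**Step 4: with calendar-month effects in the model.** This is an illustration only. The article's analysis section does not mention month effects, and the intracluster correlations used (0.001–0.05) are assumed. A generalised least squares fit to hospital-month means (about 10,500/(18 × 18) = 32 women each), with a random hospital effect, a 6-month lag and the 2-month block excluded, recovers 11–31% of the true effect with 9 steps and −4% to 10% with 6 steps. Adjusting for time while keeping the calendar rule makes the attenuation worse, because the same-month comparisons fall largely in the mislabelled months.

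**The case against.** The strongest reply is that the article never says a woman is placed in a period by her delivery date, and that several sections point the other way. Eligibility requires a visit at 11–13+6 weeks, consenting women are screened, and recruited women are followed to the endpoint. The 10 months left after 18 months of enrolment cover the 7.4–8.1 months from screening to 42 days after a 40-week delivery. The model also adjusts for screening risk, which an unscreened woman does not have. On that reading no follow-up woman is unscreened.

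This stands as far as it goes: it is not established that unscreened women will enter the analysis. It does not remove the problem. The same sections recruit only at hospitals already running the intervention, so the cohort they describe contains no controls, and baseline women would have no screening risk either. The only stated source of controls is the baseline data, which stop at each hospital's start. Women who passed the window before the start and delivered after it are then either counted as follow-up or left in neither period.

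A second reply is that detailed exposure rules belong in the analysis plan. That would answer a silence, but here the article states a comparison, and the comparison is by period.

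A reader might also infer that letting baseline end at the start of the intervention breaks the stated intention-to-treat basis, because actual start dates could define exposure. The documents do not support this: the start may equally be the scheduled one, and the order is randomised for all hospitals at one time.

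**Conclusion.** The point holds in a limited form. The comparison in Study design and setting, taken literally, does not match the gestational window in which the intervention can act, and it conflicts with the sections describing a screened cohort. With the practice-change block excluded, about 4 months (two steps) per hospital would be affected for term births, or about 19–33% of follow-up deliveries at a 6-month lag (about 16–39% for lags of 5.3–6.7 months). A simple before/after contrast at 25% would show a true risk ratio of 0.70 as about 0.78.

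These sizes are illustrative. They rest on assumed layouts, uniform deliveries and classification by delivery date. The lag is shorter for preterm births, and would also be shorter if onset dates were used.

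Two stronger readings are tempting. One is that control women will certainly be counted as intervention women; the conflicting sections leave that open. The other is that three full steps of follow-up are mislabelled; the follow-up wording places follow-up after the 2-month block, which leaves about two. What the documents do establish is that the definition of exposure for the primary comparison is unresolved, and that the stated version biases towards no effect.

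**What to change.** Reconcile Study design and setting with Participant eligibility and recruitment, Sample size and Statistical analysis, so that one population and one comparison are described, including where control women come from.

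Define each woman's condition and period by the date she reaches 11–13+6 weeks, by visit date or by gestational dating where there is no visit date. She is a control if that date falls before her hospital's randomised start and intervention if it falls on or after it, whatever her delivery date. Follow each woman to 42 days postpartum. Handle the 2-month practice-change block as one declared category. This removes the misclassification due to timing.

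The cost is small: revised wording, one derived variable, and extraction of gestational dating for baseline women. That extraction is extra work, since the article mentions crown–rump-length dating only within the intervention's risk assessment and does not show that it is collected for controls.

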**Fig. 1 Fig1:**
[figure not shown]
Preeclampsia risk prediction model for Chinese pregnant women (ChiPERM) stepped-wedge design

A randomized stepped-wedge controlled trial design is recommended for the evaluation of clinical practice change interventions as it provides a number of pragmatic and scientific advantages over a randomized controlled trial design [17, 18]. First, it provides a similar level of evidence as a standard parallel cluster randomized controlled trial. Second, although all the participated hospitals will receive the intervention, its sequential implementation across eighteen sectors provides the capacity to identify secular trends, i.e. changes over time before the intervention is implemented. Third, the design provides an opportunity for all participating services and women to receive the intervention, overcoming ethical and logistical challenges arising from withholding the intervention.

All eighteen hospitals have covered 15 provinces across mainland China. The antenatal services in the eighteen hospitals service urban and rural areas and provide care to over 100,000 women annually, accounting for approximately 1% of births in mainland China.

### Random allocation and blinding

A statistician who is independent of intervention development and implementation will randomly allocate the order in which the Bayes-theorem based preeclampsia risk prediction is implemented across the eighteen hospitals. The random sequence will be generated using a computerized random number generator with allocation undertaken for all eighteen hospitals at the one time. Study personnel involved in collecting outcome data will be blind to the allocated order of the delivery of the preeclampsia risk prediction across the hospitals. Participants providing outcome data will be informed the experimental nature of preeclampsia risk prediction across hospitals and therefore will not be blind to the stage of study occurring in the service they attend. Given the practice change nature of the preeclampsia risk prediction, clinicians in antenatal services will be aware when their service is in the intervention period.

### Participant eligibility and recruitment

During the 28-month data collection period, in the hospitals conducting this risk prediction intervention, it is intended that all pregnant women with singleton pregnancy who attend prenatal visit before 13^+6^ gestational weeks will be inquire to participate this study. Those women signing the informed consent will receive the Bayes-theorem based preeclampsia risk prediction.

The inclusion criteria are: maternal age ≥ 18 years old, singleton pregnancy, and prenatal visit between 11–13^+6^ weeks of gestational age, and agreement to the informed consent. The exclusion criteria were: multiple pregnancy, first prenatal visit after 14 weeks of gestational age, with severe fetal abnormalities, regular taking aspirin before first antenatal visit, complicated with severe psychological diseases or other diseases which are inappropriate for the study. All enrolled women have the chance to decline participating in or opting out during followup period.

### Intervention

Model of care for addressing the Bayes-theorem based preeclampsia risk prediction in first trimester will be implemented in antenatal service during 11–13^+6^ gestational weeks across the eighteen participating sectors. As shown in Fig. 2, the prediction pipeline will consist of four key elements, including Bayes-theorem based risk assessment, aspirin intervention, followup and endpoint outcomes. The inventions will be delivered to women who attend antenatal visit each month and at delivery and till 42 day postpartum.

**Fig. 2 Fig2:**
[figure not shown]
Bayes-theorem based preeclampsia risk preventive strategy

### Risk assessment

The implementation of the Bayes-theorem based preeclampsia risk prediction will be calculated by the model of The Fetal Maternal Foundation (https://fetalmedicine.org/research/assess/preeclampsia/first-trimester). This model is derived from maternal history, MAP, UTPI and serum PlGF at 11–13^+6^ weeks. Maternal history includes age, race, height, weight, gestational week based on crown rump length (CRL), pregnancy history, use of artificial reproductive technique, smoking history, history of chronic diseases (hypertension, diabetes mellitus, renal disease), adverse pregnancy history, previous history of preeclampsia, history of autoimmune diseases, pregnancy interval over 10 years, systolic blood pressure ≥ 130mmH and (or) diastolic blood pressure ≥ 80 mmHg, obstructive sleep apnea syndrome and previous history of prenatal diagnosis such as villus biopsy and amniocentesis.

The results of laboratory examination will be collected, including levels of folic acid, vitamin B12, fasting blood glucose, blood routine, urine routine, renal function, liver function, blood lipid and coagulation function. Blood pressure is measured by validated automated devices (OMRON, HBP-1320, China) according to a standardized protocol.

Uterine artery PI (UTPI) is measured by Doppler examination of uterine arteries technique in the period from 11 to 13^+6^ gestational weeks. Since this is a common time for first-trimester ultrasound examination in mainland China, UTPI measurement in this trial is practical and available. For the first-trimester transabdominal assessment of uterine artery resistance, a midsagittal section of the uterus and cervix is obtained initially. Using color flow mapping, the transducer is gently tilted sideways, in the purpose that the uterine arteries are identified with high-velocity blood flow along the side of the cervix and uterus. The pulsed-wave Doppler sampling gate should be narrow (set at approximately 2 mm) and positioned on either the ascending or descending branch of the uterine artery at the point closest to the internal cervical os, with an insonation angle < 30◦. In order to verify that the uterine artery is being examined, the peak systolic velocity should be > 60 cm/s. The PI is measured when at least three identical wave forms are obtained. Detailed methodology can be referred to the guideline and published papers [19, 20].

Serum PlGF (Aucheer C001) and sFlt-1 (Aucheer C002) were tested by immunoassay, respectively. Samples were collected by veni puncture into tubes containing ethylenediaminetetraacetic acid, centrifuged, and stored at -80℃. The most centrally located veni puncture sample within each of the 6 intervals of gestational age for each pregnant woman was used for analysis. Sample collection methods, biospecimen processing, and validation of the assays used were described in manufacturer’s handbooks.

